# Benefit of a flash dose of corticosteroids in digestive surgical oncology: a multicenter, randomized, double blind, placebo-controlled trial (CORTIFRENCH)

**DOI:** 10.1186/s12885-022-09998-z

**Published:** 2022-08-23

**Keywords:** Perioperative corticosteroids, Digestive surgical oncology, Randomized placebo-controlled trial, Postoperative morbidity, cancer-related outcomes

## Abstract

**Background:**

The modulation of perioperative inflammation seems crucial to improve postoperative morbidity and cancer-related outcomes in patients undergoing oncological surgery. Data from the literature suggest that perioperative corticosteroids decrease inflammatory markers and might be associated with fewer complications in esophageal, liver, pancreatic and colorectal surgery. Their benefit on cancer-related outcomes has not been assessed.

**Methods:**

The CORTIFRENCH trial is a phase III multicenter randomized double-blind placebo-controlled trial to assess the impact of a flash dose of preoperative corticosteroids versus placebo on postoperative morbidity and cancer-related outcomes after elective curative-intent surgery for digestive cancer. The primary endpoint is the frequency of patients with postoperative major complications occurring within 30 days after surgery (defined as all complications with Clavien-Dindo grade > 2). The secondary endpoints are the overall survival at 3 years, the disease-free survival at 3 years, the frequency of patients with intraabdominal infections and postoperative infections within 30 days after surgery and the hospital length of stay. We hypothesize a reduced risk of major complications and a better disease-survival at 3 years in the experimental group. Allowing for 5% of drop-out, 1 200 patients (600 per arm) should be included.

**Discussion:**

This will be the first trial focusing on the impact of perioperative corticosteroids on cancer related outcomes. If significant, it might be a strong improvement on oncological outcomes for patients undergoing surgery for digestive cancers.

**Trial registration:**

ClinicalTrials.gov, NCT03875690, Registered on March 15, 2019, URL: https://clinicaltrials.gov/ct2/show/NCT03875690.

**Supplementary Information:**

The online version contains supplementary material available at 10.1186/s12885-022-09998-z.

## Background

Inflammation is harmful in cancer patients, especially in those undergoing surgery. It increases the risk of postoperative complications, time to recovery, hospital length of stay and impairs cancer-related outcomes (recurrence and survival) [1–7]. High preoperative levels of C-reactive protein and pro inflammatory adipocytokines are associated with a higher risk of postoperative morbidity in colorectal cancer surgery [8–10]. Perioperative inflammation is also a predictor of poorer survival in patients operated for digestive cancer whether complications occur or not [11–19]. So, the modulation of surgery-induced inflammation seems crucial to improve cancer survival.

The effects of a preoperative high dose of corticosteroids (flash) over the inflammatory markers have been established in different surgical fields [20–25], as well as its safety, namely in digestive surgery regarding the onset of anastomotic leakage and surgical site infection [20, 22–24]. Two systemic reviews and meta-analyses showed that perioperative corticosteroids decreased inflammatory markers and were associated with a diminution until 50% of the risk of some postoperative complications after esophageal, liver, pancreatic and colorectal surgery [24, 25]. Regarding the dose used, a few studies have used dexamethasone or hydrocortisone at low doses [26, 27], but most of the trials have used methylprednisolone at high doses, ranging between 500 mg independently of the patient’s weight to 30 mg/kg [24, 25, 28–34].

In most studies, the main endpoint was the concentration of inflammatory markers [24, 25] with little attention paid to clinically pertinent criteria or the prognosis of cancer, although the literature suggests that reducing the incidence of severe complications will improve the oncological outcomes [7, 8, 29, 30].

Thus, a prospective randomized controlled trial is warranted in order to evaluate the safety and the benefit of a flash dose of corticosteroids on postoperative morbidity and cancer-related outcomes after surgery for digestive cancer.

## Methods/design

### Protocol overview

The CORTIFRENCH trial is a phase III, multi center, randomized, double-blind, placebo-controlled trial to assess the superiority of a flash dose of preoperative corticosteroids on the reduction of major complications after digestive surgical oncology. Patients likely to be included in this trial will be randomized in a 1:1 ratio between two groups: an experimental group receiving 20 mg/kg of methylprednisolone intravenous at the time of anesthesia induction and a control group receiving an intravenous placebo with an identical aspect. All members of the anesthesiology and surgical team will be unaware of the group assignments, as well as the investigator and the medical team managing the patient and recording the outcomes. Major complications (Clavien-Dindo grade > 2) [35] occurring within 30 days after surgery, postoperative and intra-abdominal infections at postoperative day 30 (D30) will be recorded and overall and disease-free survival at 3 years will be evaluated in order to assess if a flash dose of preoperative corticosteroids has a real impact on the onset of postoperative complications, recovery and cancer-related outcomes after digestive cancer surgery. The flowchart of the study has been reported in Fig. 1.

**Fig. 1 Fig1:**
[figure not shown]
Flowchart of the trial

### Objectives

The primary objective is to assess the impact of a flash dose of preoperative corticosteroids versus placebo on the onset of major complications (Clavien-Dindo > 2) [35] within 30 days after elective curative-intent surgery for digestive cancer.

Secondary objectives are to assess the safety of a preoperative flash of corticosteroids versus placebo and its influence on postoperative and intra-abdominal infections at D30, hospital length of stay and 3-year overall and disease-free survival.

### Inclusion criteria

Inclusion criteria are patients older than 18 years old, undergoing elective surgery for a digestive cancer (except purely hepatic surgery), operated in a curative intent, affiliated to the French National Health System and providing their written informed consent.

### Exclusion criteria

Patients with any of the following criteria will not be included in the study: emergency surgery, palliative surgery, exclusive liver surgery, surgery with concomitant hyperthermic intraperitoneal chemotherapy, pregnant or breastfeeding women, ASA score > 3, long-term ongoing oral treatments with steroids, a contra-indication to steroids therapy (active infection, ongoing viral disease, uncontrolled psychotic state, hyper sensitivity to methylprednisolone or to one of his excipients), impossibility to adhere to the medical follow-up of the trial for geographical, social or psychological reasons, patients subject to a measure of legal protection (guardianship, tutorship) and persons subject to a court order. Patients with live vaccine or live attenuated vaccine administered within 1 month before surgery and cancelled surgery without deferral will be secondary excluded.

### Endpoints

The primary endpoint is the frequency of patients with postoperative major complications occurring within 30 days after surgery (D30). Major complications are defined as all complications with Clavien-Dindo grade > 2 [35].

Secondary endpoints are:

the overall survival at 3 years (defined as the time from surgery to death from any cause),the disease-free survival at 3 years (defined as the time from surgery to first documented progressive disease or death from any cause, whichever occurs first),the frequency of patients with postoperative infections occurring within 30 days after surgery and defined according to the CDC (Centers for Disease Control and Prevention) definitions,the frequency of patients with intra-abdominal infections (including anastomotic fistula and intraabdominal abscess) within 30 days after surgery and defined according to the CDC definitions,the hospital length of stay (in the case of death, the patient will be considered as hospitalized until D30),the frequency and the type of side effects, particularly hyperglycemia, electrolyte disorders and wound healing assessed respectively by glycemia and electrolyte panel within the first 24 postoperative hours and clinical inspection at D30 follow-up visit.

### Randomization

Eligible patients will be identified at the preoperative consultation with the surgeon. If the patient meets the eligible criteria, the investigating doctor will present the study. The patient will have a reflection period after the consultation and will be informed of his/her right to withdraw consent at any time without prejudice and without having to justify this decision. After receiving the written informed consent and after verification of the inclusion criteria, the patient will be included.

Patients will be randomized in a 1:1 ratio between 2 groups receiving either 20 mg/kg of intravenous methylprednisolone (experimental group) or an identical-aspect intravenous placebo (control group) at the time of anesthesia induction.

Randomization will be performed online by the investigator using the secure CleanWeb platform at the time of inclusion and stratified on the center, the site of surgery (upper digestive/pancreatic or colorectal cancer) and the surgical approach (scheduled laparoscopic or open surgery).

### Blinding process

To maintain a double-bind trial, all members of the anesthesiology and surgical team will be unaware of the group assignments. Only the pharmacy of each participating center will know the randomization group in order to prepare the bag to be infused and deliver it to the anesthesiology team. If the pharmacy is not able to prepare the allocated treatment for logistical reasons, a member of the nursing staff will be authorized to carry out the preparation. Then, this person will not be involved in the follow-up of the patient to maintain the double blind.

Blind may be lifted in case of unexplained or possible toxic death, in case of a serious adverse event when the knowledge of the product administered is necessary for the care of the patient and if the medical care is different depending on the treatment receive, in the event of accidental or intentional taking by a person other than the participant tested and in the case of a suspected unexpected serious adverse reaction for the purpose of transmission to authorities.

### Treatment methods

Patients randomized in the experimental group will receive 20 mg/kg intravenous methylprednisolone infused in a ready-to-use 50 mL bag of sodium chloride 0.9% during 30 min at the time of anesthetic induction.

Patients randomized in control/placebo group will receive 50 mL of intravenous sodium chloride 0.9% in a ready-to-use bag during 30 min at the time of anesthetic induction. As methylprednisolone is colorless, bags containing sodium chloride alone or sodium chloride plus methylprednisolone will identical aspect.

Live vaccines or live attenuated vaccines will be contra-indicated during the month preceding surgery and until 3 months later.

### Surgical management

#### Pre-operative check-up

Each institution will prepare patients and scheduled surgery according to its own institutionally validated protocols. All patients included will undergo the preoperative evaluation currently performed at each institution. Preoperative immunonutrition will not be mandatory but its use will be recorded.

#### Intraoperative management

At the time of the anesthesia induction, methylprednisolone or placebo will be administrated according to the randomization group. Diabetics patients will be closely monitored in both groups during and immediately after surgery by capillary glycemia every 3 h in order to adjust insulin therapy as appropriate. Patients considered at risk for postoperative nausea and emesis will receive a single preoperative dose of 4–8 mg of dexamethasone intravenous (equivalent to 20–40 mg of methylprednisolone), following the guidelines of the French Society of Anesthesiology and Reanimation (SFAR). This information will be recorded.

#### Postoperative management

Clinical and biological follow-up (blood samples) will be performed according to the protocols of each institution. The only specific requirement of the study will be an electrolyte panel and fasting glycemia performed within the first 24 h after surgery in order to detect a possible effect of corticosteroids. The postoperative management, monitoring and follow-up will be as usual according to each institution’s current practices, but each participating center will be asked to record the following data: day of oral refeeding, mean daily pain visual analog scale, onset of fever or any complication (whether infectious or not), laboratory and imaging studies performed between surgery and postoperative day 30.

### Follow-up

According to each center’s protocol, a D30 visit will be scheduled between postoperative days 28 and 45. Patients will undergo a clinical evaluation by the surgeon and will be asked about any events occurring since the initial hospital discharge. Any complications occurred since the initial discharge or detected during the examination will be recorded. In case of re-hospitalization between hospital discharge and the scheduled follow-up visit at postoperative D30, all data related to any complications will be collected. Dead patients will be considered to have been hospitalized between the date of death and postoperative D30.

The study will end at 3 years. At the end of the study, vital status (including date and cause of death if appropriate) and information about disease progression (including the date of discovery in case of recurrence) will be collected and recorded for all included patients.

### Data collection

The data will be entered into an e-CRF (electronic Case Report Form) specifically developed for this study using a Clinical Data Management System (CMDS-CleanWeb). All required information for the study will be entered as and when it is obtained. Thanks to automatic checks, in case of missing or inconsistent data, request for correction will be sent to participating centers via the CMDS. If corrections are necessary, they will be made directly using the CMDS. At the end of the study, a blind review of data will be performed and in case of additional queries, it should be resolved before the final database lock.

### Statistical analysis and sample size

This study is a phase III multi center randomized double blind placebo-controlled trial. According to the literature, the incidence of major complications at D30 after surgery is 26% [36]. We hypothesized this proportion will decrease to 18% in patients with corticosteroids administration. Based on these hypotheses with an alpha risk of 5% and a power of 90% and including an interim analysis at the half of the inclusions, 1184 analyzable patients (592 per arm) are required. Allowing for 5% of drop-out, 1200 patients (600 per arm) will be included. Statistical analyses will be performed at the coordinating center (INSERM CIC 1432 of Dijon).

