#### Interim analysis

One interim analysis will be performed after the inclusion of 592 patients (296 per arm). The interim analysis will assess the superiority of the experimental arm versus the control group for the primary endpoint: early termination will be considered only if superiority is met. The interim analysis will have a two-sided alpha level of 0.0003. According to the O’Brien-Fleming spending rule [37], this will leave a two-sided alpha level of 0.049 for the final analysis. The data safety monitoring board will decide if the trial should be stopped according to the results of the interim analysis.

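### The sample-size figures do not reconcile: 1200 inclusions with 5% drop-out leave 1140 analysable patients, 44 fewer than the 1184 stated as required.

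*Protocol article*

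**What the plan says.** In the protocol article, the section on statistical analysis and sample size takes a major-complication rate of 26% at day 30 from the literature and adds: "We hypothesized this proportion will decrease to 18% in patients with corticosteroids administration". With alpha 5%, power 90% and one interim analysis at half of the inclusions, it concludes that "1184 analyzable patients (592 per arm) are required". The next sentence gives the enrolment target: "Allowing for 5% of drop-out, 1200 patients (600 per arm) will be included".

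The Methods paragraph of the abstract repeats the last step: "Allowing for 5% of drop-out, 1 200 patients (600 per arm) should be included".

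Two other sections bear on the check. The interim-analysis section sets the look at 592 inclusions (296 per arm) and says of the alpha spent there that "this will leave a two-sided alpha level of 0.049 for the final analysis". The main-analysis section names a chi-square test and mentions no continuity correction. The article gives no other drop-out rate and no explanation of the step from 1184 to 1200.

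**The concern.** A 5% allowance on 1184 should add about 60 patients; the plan adds 16. Either the enrolment target is too small for the stated requirement, or the allowance is not 5%, or 1184 is not the number of analysable patients.

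These are the figures against which readers, the ethics committee and the data safety monitoring board will judge whether the trial met its plan. If drop-out is exactly what the plan assumes, the trial will report 1140 analysable patients against a published requirement of 1184 and will appear to have missed its own target. The article describes recruitment as ongoing. A clarification made now, before the final analysis, raises no question; one made after the results are known would look post hoc.

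**Working it through.** **Inputs.** From the sample-size section: p1 = 0.26, p2 = 0.18, power 0.90, alpha 0.05, 1184 required (592 per arm), drop-out d = 5%, 1200 included (600 per arm). From the interim-analysis section: two-sided final alpha 0.049. Allocation is 1:1 (randomization section).

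**Step 1: where 1184 might come from.** The pooled two-proportion formula, with mean rate 0.22, is

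n per arm = [z(1−α/2)·√(2 × 0.22 × 0.78) + z(0.90)·√(0.26 × 0.74 + 0.18 × 0.82)]² / 0.08²

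| Version, two-sided | n per arm | Total, rounded up per arm |
|---|---|---|
| Uncorrected, alpha 0.05 | 561.4 | 1124 |
| Uncorrected, alpha 0.049 | 564.4 | 1130 |
| Continuity-corrected, alpha 0.05 | 586.1 | 1174 |
| Continuity-corrected, alpha 0.049 | 589.1 | 1180 |

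Read as an analysable number, 1184 is close to the continuity-corrected results (within 1%), but none of these versions gives it exactly. There is another route: the uncorrected 562 per arm divided by 0.95 is 591.6, so 592 per arm and 1184 in total. On that route the 5% is already inside 1184.

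**Step 2: from 1184 to the number to include.**

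- Standard inflation, N/(1 − d): 1184/0.95 = 1246.3, so 1247 (1248 with equal arms, 624 each).
- The cruder N × (1 + d): 1184 × 1.05 = 1243.2, so 1244 (622 per arm).

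Neither gives 1200, and rounding does not bridge a gap of 44 to 48 patients.

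**Step 3: from 1200 back to the analysable number.**

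- 1200 × 0.95 = 1140 (570 per arm); 1184 − 1140 = 44.
- Drop-out actually covered: (1200 − 1184)/1200 = 16/1200 = 1.33%.

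**Step 4: power at each analysable number.** Power = Φ{[0.08 − c − z(1−α/2)·√(2 × 0.22 × 0.78/n)] / √(0.34/n)}, where 0.34 = 0.26 × 0.74 + 0.18 × 0.82, alpha is 0.049, and c = 0 (uncorrected) or 1/n (continuity-corrected).

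| Analysable | n per arm | Uncorrected | Continuity-corrected |
|---|---|---|---|
| 1184 | 592 | 91.3% | 90.1% |
| 1140 | 570 | 90.3% | 89.0% |

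**Step 5: a related sign.** The sample-size section puts the interim at half of the inclusions, and the interim-analysis section puts it at 592 inclusions. Half of 1200 is 600; 592 is half of 1184. So the article uses 1184 once as the analysable number and once as if it were the number included.

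**The case against.** The strongest reply is that 1184 may already be the inflated figure. The uncorrected formula at alpha 0.05 gives 562 per arm, and dividing by 0.95 gives exactly 592. On that reading 1200 is a rounding, enrolment is adequate, there is no 44-patient shortfall, and the only wrong word is the one calling the 1184 analysable. This is plausible, and it fits 592 better than the continuity-corrected route, which the named test does not call for. But the article does not say it, and the sentence would still be wrong as printed. The shortfall against 1184 is therefore conditional on the label being right; the contradiction between the printed figures is not.

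A second reply is that drop-outs need not leave the main analysis. It is by intention to treat, and patients lost to follow-up are first counted under a worst-case assumption and only afterwards excluded. So 1140 describes the analysis with exclusions. That is fair, but the sample-size section itself separates analysable from included patients and makes a drop-out allowance between them, and its figures must agree on those terms.

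A third reply is that little is lost: about one percentage point of power, and still above 90% with the uncorrected test. This stands. It limits the consequence but does not make the figures consistent.

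**Conclusion.** The point holds. The figures of 1184 analysable, 5% drop-out and 1200 included contradict each other, and the abstract repeats the last two. If 1184 is the analysable requirement, the target is 44 patients short after 5% drop-out, or equivalently the allowance is 1.33%. If 1184 already includes drop-out, it is mislabelled. The article does not allow a choice between the two.

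This is an error in headline planning figures, not evidence of an underpowered trial: at 1140 analysable patients, power is 90.3% uncorrected or 89.0% continuity-corrected. Those figures assume the plan's own rates of 26% and 18%, equal loss in both arms, and a single final test at two-sided alpha 0.049.

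**What to change.** Restate the figures so that they agree, without enrolling more patients. A wording that is true whatever the origin of 1184: *1200 patients will be included; with 5% drop-out, 1140 (570 per arm) are expected to be analysable, giving about 90% power with an uncorrected chi-square test (89% with continuity correction) at a final two-sided alpha of 0.049.*

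Alongside this, the sponsor should name the formula behind 1184 and say whether that number is before or after drop-out:

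- If 1184 already includes the 5%, remove the analysable label and give the uninflated number.
- If 1184 is truly the analysable requirement and is to be kept, say that 1200 allows for only about 1.3% drop-out. This alternative should not be used unless that origin is confirmed, since it could replace a correct 5% with a wrong figure.

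Correct the abstract in the same way, and say which total the 592 patients at the interim are half of. The cost is a wording change in the protocol and analysis plan. The stated analysable number becomes smaller and the stated power margin slightly less favourable; the hypothesis, the test, the alpha levels and the enrolment target do not change.

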#### Demographics and baseline characteristics

Patient’s characteristics at baseline will be described in terms of frequencies for categorical variables and in terms of means (+/- standard deviation) or medians (interquartile range) for continuous variables. These characteristics will be compared between groups using Chi squared (or Fisher’s exact test) or t-Test (or Mann-Whitney test) when appropriate.

